### Data collection methods

The data collection schedule is shown in Table 1. Subjects will be asked to wear a wristband wearable device. On day 7 of each wearing period, (1) the SCID-5 will be used to assess whether the subjects meet the criteria for a depressive episode as defined by the DSM-5 and (2) the HAMD will be used to assess the severity of the depressive episode. These evaluations will be tied to the wearable device data that is being acquired at the same time. A maximum of five evaluations will be conducted per subject, with seven consecutive days regarded as a single evaluation period. The Silmee W22 (TDK Corporation, Tokyo, Japan) wearable device, which is commercially available as a non-medical device, will be used in this study. Body movement and sleep time can be calculated from the Silmee’s accelerator data. Heart rate and heart rate variability can also be measured by processing pulse wave signals collected by Silmee’s photoplethysmographic sensor.

**TABLE 1 T1:** Schedule for data collection and evaluations during the observation period.

Assessment^a^	Visit 0 (Baseline)	Visit 1	Visit 2	Visit 3	Visit 4	Visit 5
Outpatients	Conducted on a regular outpatient basis					
Inpatients	Conducted at least one week apart; after hospital discharge, conducted during outpatient visits					
Healthy subjects	Conducted about once a month (approximately)					
Wearable devices	Wearing the Silmee for at least 7 days prior to the next visit during the study period					
Obtaining consent	◯					
Patient background	◯					
SCID (Patients only)	◯^b^		△	△	△	△
DSM-5 with or without depressive episode (SCID depressive episode part only)		◯	◯	◯	◯	◯
M.I.N.I (Healthy subjects only)	◯	△	△	△	△	△
Clinical Global Impression of illness Severity (CGI-S) (Patients only)		◯	◯	◯	◯	◯
HAMD17		◯	◯	◯	◯	◯
MADRS		◯	◯	◯	◯	◯
YMRS		◯	◯	◯	◯	◯
BDI-II		◯	◯	◯	◯	◯
Concomitant medications						

^a^During the study period, assessment periods will be conducted one to five times per research subject. Therefore, Visits 2, 3, 4, and 5 may not be conducted, depending on the research subjects.

^b^Since it takes time to fully implement the SCID, it will be performed at either visit 0 or visit 1, depending on the convenience and desires of the subject.

△This evaluation will not necessarily be performed every time but will be re-performed as needed (for example, when new symptoms appear or when the diagnosis changes).

“◯” Means that the assessment is to be performed.

The Silmee W22 is capable of calculating the pace of walking or running using acceleration data from a 3-axis accelerometer. The data from the Silmee W22 will be transmitted to cloud storage *via* a dedicated app. The only information that will be uploaded to the cloud will be the device number of the Silmee W22 paired with the dedicated app and the data collected through the Silmee W22. Subjects will be asked to install the dedicated app on their own smartphones and to keep it open or to open it at least once every 3 days.

In this study, electronic data capture (EDC) will be used to collect information such as the date of consent, patient background, SCID diagnosis name, symptom rating scale results, and concomitant medications. We will use “cubeCDMS” from CRScube Inc., for the EDC.

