### Research objectives

The general objective of this study is to build a machine learning model that can be implemented as software in a wearable device to detect depressive episodes in subjects with depressive symptoms and to quantify the severities of such episodes. Our specific objectives are: (1) to obtain triaxial acceleration data, pulse rate, skin temperature, and ultraviolet light data from patients with depressive symptoms and from healthy subjects who have been asked to wear a wristband wearable device; (2) to make diagnoses using the Structured Clinical Interview for DSM-5 (SCID-5) and severity assessments using HAMD and to correlate these diagnoses with the collected data; and (3) to construct an optimal learning model enabling the detection of depressive episodes and the evaluation of depressive episode severity by applying machine learning to the collected data set.

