## Methods and analysis

### Trial design and setting

This study will be an open-label observational study. Patients who meet the inclusion criteria will be recruited at the time of their outpatient visit to Keio University Hospital or other medical facilities or during their hospitalization, and healthy individuals without a history of mental illness will be recruited through recruitment advertisements on a website. Patient recruitment will be conducted at the following locations and medical facilities: Tokyo (Keio University, Akasaka Clinic, Oizumi Hospital, Oizumi Mental Clinic, and Tsurugaoka Garden Hospital); Kanagawa (Nagatsuta Ikoinomori Clinic); Fukushima (Asaka Hospital); and Yamagata (Sato Hospital). Other medical facilities may be added depending on the recruiting situation.

In this study, patients with depressive symptoms (depressive disorder, bipolar disorder and related disorders, anxiety disorders, obsessive-compulsive and related disorders, trauma- and stressor-related disorders, dissociative disorders, or somatic symptoms and related disorders) and healthy subjects will wear a wristband wearable device up to five times for 7 days at a time. The timing of the start of the measurement period and the interval between each 7-day cycle will differ for each subject.

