### Eligibility criteria

The inclusion criteria for patients shall be as follows: (1) a clinical diagnosis of depressive disorder, bipolar or related disorder, anxiety disorder, obsessive-compulsive or related disorder, trauma-and stressor-related disorder, dissociative disorder, or somatic symptom or related disorder according to the DSM-5 criteria, the presence of depressive symptoms, and an outpatient or inpatient status at Keio University Hospital or another medical facility participating in the study; (2) an age of 18 years or older at the time of consent; (3) confirmation from a psychiatrist that the subject is capable of providing written consent or that a guardian can provide consent if the psychiatrist determines that obtaining consent from the patient will be difficult; and (4) ownership and ability to use a smart phone (iOS 11. 0 or later or Android version 5.0 or later). The inclusion criteria for healthy subjects shall be as follows: (1) no history of psychiatric illness and cooperation with the study on a volunteer basis (after obtaining consent, the M.I.N.I. will be used to confirm that the subject does not have a psychiatric illness); (2) an age of 18 years or older at the time of consent; and (3) ownership and ability to use a smartphone (iOS 11.0 or later or Android version 5.0 or later).

The exclusion criteria for patients shall be as follows: (1) an inability to complete measurements that could affect their medical conditions, as determined by a psychiatrist; (2) the presence of comorbidities that could affect the measurement results, such as paralysis of the upper limbs; and (3) ineligibility for other reasons determined by the principal investigator or sub-investigator. The exclusion criteria for healthy subjects shall be as follows: (1) the presence of comorbidities that could affect the measurement results, such as paralysis of the upper limbs; and (2) ineligibility for other reasons determined by the principal investigator or sub-investigator. Researchers will obtain written informed consent from all the participants. The participants will be able to leave the study at any time.

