### Statistical methods

All research subjects will be included in the analysis. The data from the Silmee W22 will be denoised and feature-engineered to create a machine learning algorithm that is highly correlated with the presence and severity of depressive episode ratings obtained during researcher-conducted interviews with the subjects. For denoising, we will use techniques such as Continuous Decomposition Analysis (CDA), Discrete Decomposition Analysis (DDA), Gaussian filters, and an adaptive color threshold. These methods are not limited to raw data. If a more suitable method for denoising the raw data becomes available, that method will be used. For feature engineering, we will use autocorrelation, cross-correlation, and other analysis methods to extract temporal structures and patterns for data with time delays. Regarding the feature engineering for heart rate variability, parameters such as standard deviation of normal-to-normal intervals (SDNN), root mean square of successive differences (RMSSD), standard deviation of successive RR interval differences (SDSD), NN50, and Estimated Breath Cycle (EBC) will be used as time-domain features, and low-frequency (LF) and high-frequency (HF) peaks, LF and HF power, normalized LF and HF power, LF/HF ratio, etc., will also be used. In addition, we will search for other features that are useful for improving accuracy and will use the optimal methods available.

For machine learning algorithms, we will use meta-models such as Support Vector Machine (SVM), Support Vector Regression (SVR), Gradient Boosting Classification/Regression, and so on; alternatively, we will use Deep Learning to find the method that gives the highest accuracy. The significance level will be set at 0.05.

In addition, structural brain information and brain functional connectivity from collaborators who participated in another study, “Longitudinal MRI study Identifying the Neural Substrates of Remission/Recovery in Mood Disorders” (Approval Number: 20190239) at Keio University and who also participated in this study will be provided to this study. We will conduct an exploratory analysis using biostatistics and machine learning to examine the relationship between the results of an analysis of structural brain information and brain functional connectivity and the amount of daily life activity and other data obtained from the wearable devices.

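### Inpatient and outpatient weeks are pooled and the method is chosen for accuracy, so the model can partly learn care setting instead of depressive state

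*Protocol article*

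**What the plan says.** **Who enters.** Under Trial design and setting, patients are "recruited at the time of their outpatient visit to Keio University Hospital or other medical facilities or during their hospitalization", while healthy subjects come through website advertisements. The Eligibility criteria treat the two care settings as one category: "the presence of depressive symptoms, and an outpatient or inpatient status at Keio University Hospital or another medical facility participating in the study".

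**When they are measured.** Table 1 (Data collection methods) gives inpatients their own row: "Conducted at least one week apart; after hospital discharge, conducted during outpatient visits". A person enrolled in hospital can therefore contribute data sets from the ward and, later, from home. The Sample size section adds that severity usually falls over follow-up, even when it was high at the start.

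**What is measured.** The Research objectives list acceleration, pulse, skin temperature and ultraviolet data, and Data collection methods notes: "Body movement and sleep time can be calculated from the Silmee’s accelerator data".

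**How it is analysed.** Statistical methods states "All research subjects will be included in the analysis", and the choice among algorithms ends with "we will use Deep Learning to find the method that gives the highest accuracy". Recruitment targets in the Sample size section are set by diagnosis (220, 40 and 40), not by care setting. The limitations in the Discussion do not mention care setting.

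**The concern.** A ward plausibly limits walking, alters sunlight exposure and regulates bedtimes. Activity, sleep timing and ultraviolet light are among the quantities the device supplies. If inpatient weeks are also more often weeks in an episode, setting and label are associated across people. Because a patient can be discharged as severity falls, they can also be associated within a person. A search for the highest pooled accuracy rewards any signal that predicts the label, including a signature of the ward.

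Three uses of the results could be affected:

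- **Referral.** The Introduction expects clinicians outside psychiatry and occupational physicians to use the model as a basis for referral. Pooled performance that draws on the contrast between ward and home can be too favourable for that use.
- **Change over time.** The Discussion expects treatment effects to become easier to detect. A predicted HAMD that drops on discharge could look like sensitivity to change.
- **Sample size adaptation.** Interim accuracy is to move the target number up or down. If setting raises that accuracy, it could support a smaller study than the intended use needs.

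**Working it through.** **The plan's own figures.** No stated figure concerns care setting. The subject total checks: 220 + 40 + 40 = 300. The 500, 650 and 800 data sets are read from learning curves whose figures are not shown, so they cannot be recomputed.

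**How much could setting alone explain?** The documents give neither the inpatient share nor episode rates by setting. All inputs below are assumptions. Let h be the inpatient share of data sets, a the episode rate in inpatient data sets, and b the rate in all others (healthy subjects included). The rule calls every inpatient week an episode and every other week not.

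- Accuracy of the rule = h·a + (1 − h)(1 − b)
- Prevalence p = h·a + (1 − h)·b; majority-class accuracy = max(p, 1 − p)

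| h | a | b | Setting only | p | Majority class | Gain |
|---|---|---|---|---|---|---|
| 0.2 | 0.8 | 0.25 | 0.16 + 0.60 = 0.76 | 0.36 | 0.64 | 0.12 |
| 0.2 | 0.8 | 0.35 | 0.16 + 0.52 = 0.68 | 0.44 | 0.56 | 0.12 |
| 0.2 | 0.9 | 0.25 | 0.18 + 0.60 = 0.78 | 0.38 | 0.62 | 0.16 |
| 0.2 | 0.9 | 0.35 | 0.18 + 0.52 = 0.70 | 0.46 | 0.54 | 0.16 |
| 0.3 | 0.8 | 0.25 | 0.24 + 0.525 = 0.765 | 0.415 | 0.585 | 0.18 |
| 0.3 | 0.8 | 0.35 | 0.24 + 0.455 = 0.695 | 0.485 | 0.515 | 0.18 |
| 0.3 | 0.9 | 0.25 | 0.27 + 0.525 = 0.795 | 0.445 | 0.555 | 0.24 |
| 0.3 | 0.9 | 0.35 | 0.27 + 0.455 = 0.725 | 0.515 | 0.515 | 0.21 |

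Setting-only accuracy runs from 68% to 80% and the gain from 12 to 24 points at the corners. Majority-class accuracy runs from 50% to 64%; the lower end lies inside the ranges, for example h = 0.3, a = 0.85, b = 0.35 gives p = 0.255 + 0.245 = 0.50.

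**Small inpatient share.** When p is below 0.5 the gain reduces to h(2a − 1). At h = 0.05 this is 0.05 × 0.6 = 0.03 for a = 0.8 and 0.05 × 0.8 = 0.04 for a = 0.9. With a = 0.7 it is 0.05 × 0.4 = 0.02. The gain is then 2 to 4 points.

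**HAMD.** Assume a within-setting SD s = 6 and a mean difference d between settings. Then r = √[d²h(1 − h) / (d²h(1 − h) + s²)].

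| h | d = 4 | d = 8 | d = 12 |
|---|---|---|---|
| 0.05 | 0.14 | 0.28 | 0.40 |
| 0.2 | 0.26 | 0.47 | 0.62 |
| 0.3 | 0.29 | 0.52 | 0.68 |
| 0.4 | 0.31 | 0.55 | 0.70 |

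For example, h = 0.3 and d = 8: 64 × 0.21 = 13.44, and √(13.44 / 49.44) = 0.52.

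**Against the targets.** In none of these scenarios does setting alone reach the 90% accuracy or the correlation of 0.85 that the Sample size section aims for. The calculation also credits the device with recovering setting perfectly, which it may not do.

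**The case against.** **Intended use.** The Introduction names psychiatrists as users, for diagnostic decisions, before it names the referral users. Inpatients belong to that use, and their data are legitimate. This stands. A reader might infer that outpatient performance should be the only main result; the documents do not support that. The outpatient stratum is needed for referral claims only.

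**Missing detail or bad design.** Strata and benchmarks are often left to an analysis plan, which is not shown here and may deal with setting; including all subjects does not rule out reporting by setting. That is fair, and the point does not rest on an absent subgroup table. It rests on what is stated: a mixed-setting population, a schedule that lets setting change with severity, and selection for accuracy.

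**Size.** Every input to the illustration is assumed. The Discussion expects few severely ill participants, which makes a large share of ill inpatients less certain. This stands, so the size is unknown. A reader might set the 68–80% beside the earlier study's 76% and infer that setting explains that result. The inpatient share of that study is not given, so the inference has no basis.

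**Mechanism.** That hospital stay changes these signals is an inference the documents do not test. The device records skin temperature, not room temperature, and pulse and heart rate variability features need not follow setting in the same way. Depressed outpatients, and any inpatient weeks without an episode, further limit how well setting can stand in for the label. A reader might infer that the model would detect hospital instead of depression; only a partial substitution is supportable.

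**Conclusion.** The concern holds in a limited form. Followed as described, the plan can credit care setting as detection of depression, and pooled accuracy and HAMD correlation can be too favourable for the referral use. Apparent sensitivity to change can partly reflect discharge. The documents do not show that the pooled figures are biased upward, only that they can be.

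The size cannot be determined without the inpatient share and the episode rates by setting. It could be a few points of accuracy if inpatient data sets are rare, or 12 to 24 points over the majority class at the corners of the assumed 20–30% range. The conclusion rests on two assumptions: that hospital stay alters the device signals, and that inpatient weeks are more often weeks in an episode. Both are plausible, and neither is tested in the documents. The point merits a change in recording and reporting, not in who is recruited.

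**What to change.** 1. Record care setting for each 7-day data set, with a code for weeks that contain a discharge. The article does not show that this is recorded: patient background is marked at Visit 0 only, whereas setting can change later.
2. Report both primary performance measures separately for outpatient and inpatient data sets beside the pooled result, and state where the healthy subjects' data sets are counted. Base any claim about referral use on the outpatient stratum.
3. Fit a reference model with no device data, using setting and the basic background already collected, on the same folds formed by subject. Report the device model's gain over it for both measures.
4. Optionally, repeat the analysis without the ultraviolet feature as a sensitivity analysis.

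The cost is one data field if setting is not already captured, some analysis wording, less precision within each stratum, and possibly a lower headline figure. No further subjects or visits are needed.

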### Data management

The data acquired by Silmee W22 is collected in a form that does not identify individuals. These data will be uploaded to the Silmee Connect cloud managed by TDK Corporation. *Via* the free application “Silmee Connect” from TDK Corporation downloaded to the smartphones of the participating study participants. The data uploaded to TDK Cloud will be transferred to the cloud for this research managed by i2medical LLC, while being linked to the device number of the Silmee W22. These data are then downloaded to i2medical LLC’s secure local environment for analysis.

The database will be constructed using the EDC system (cubeCDMS) with the support of CRScube and the Data Science Division of CMIC Corporation, the outsourcing facility, and the system will be equipped with strict security management, including data backup and access rights management. Clinical data obtained through this research will be managed and stored using the EDC system, and will be passed on to researchers at i2medical LLC and Keio University.

### Statistical methods

All research subjects will be included in the analysis. The data from the Silmee W22 will be denoised and feature-engineered to create a machine learning algorithm that is highly correlated with the presence and severity of depressive episode ratings obtained during researcher-conducted interviews with the subjects. For denoising, we will use techniques such as Continuous Decomposition Analysis (CDA), Discrete Decomposition Analysis (DDA), Gaussian filters, and an adaptive color threshold. These methods are not limited to raw data. If a more suitable method for denoising the raw data becomes available, that method will be used. For feature engineering, we will use autocorrelation, cross-correlation, and other analysis methods to extract temporal structures and patterns for data with time delays. Regarding the feature engineering for heart rate variability, parameters such as standard deviation of normal-to-normal intervals (SDNN), root mean square of successive differences (RMSSD), standard deviation of successive RR interval differences (SDSD), NN50, and Estimated Breath Cycle (EBC) will be used as time-domain features, and low-frequency (LF) and high-frequency (HF) peaks, LF and HF power, normalized LF and HF power, LF/HF ratio, etc., will also be used. In addition, we will search for other features that are useful for improving accuracy and will use the optimal methods available.

For machine learning algorithms, we will use meta-models such as Support Vector Machine (SVM), Support Vector Regression (SVR), Gradient Boosting Classification/Regression, and so on; alternatively, we will use Deep Learning to find the method that gives the highest accuracy. The significance level will be set at 0.05.

In addition, structural brain information and brain functional connectivity from collaborators who participated in another study, “Longitudinal MRI study Identifying the Neural Substrates of Remission/Recovery in Mood Disorders” (Approval Number: 20190239) at Keio University and who also participated in this study will be provided to this study. We will conduct an exploratory analysis using biostatistics and machine learning to examine the relationship between the results of an analysis of structural brain information and brain functional connectivity and the amount of daily life activity and other data obtained from the wearable devices.

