**Methods and analysis:**

Patients with depressive symptoms and healthy subjects will wear a wristband-type wearable device for 7 days; data on triaxial acceleration, pulse rate, skin temperature, and ultraviolet light will be collected. On the seventh day of wearing, the severity of depressive episodes will be assessed using Structured Clinical Interview for DSM-5 (SCID-5), Hamilton Depression Rating Scale (HAMD), and other scales. Data for up to five 7-day periods of device wearing will be collected from each subject. Using wearable device data associated with clinical symptoms as supervisory data, we will explore and build a machine learning model capable of identifying the presence or absence of depressive episodes and predicting the HAMD scores for an unknown data set.

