### Primary outcomes

The primary outcome measures will be the machine-learning algorithm’s estimation of whether the patient meets the DSM-5 definition of a depressive episode and the HAMD machine-learning algorithm’s total score estimate.

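### Algorithm and features are chosen by highest accuracy, but no evaluation data are defined apart from that choice, so the reported performance may be optimistic by roughly 1 to 5 points

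*Protocol article*

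**What the plan says.** All references are to the protocol article.

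- **Primary outcomes.** These are model outputs: "the machine-learning algorithm’s estimation of whether the patient meets the DSM-5 definition of a depressive episode", and the model's estimate of the HAMD total score.
- **Statistical methods, algorithms.** The candidate list is open: "we will use meta-models such as Support Vector Machine (SVM), Support Vector Regression (SVR), Gradient Boosting Classification/Regression, and so on". The choice rule follows: "alternatively, we will use Deep Learning to find the method that gives the highest accuracy".
- **Statistical methods, features.** After a list of named features, the text adds that "we will search for other features that are useful for improving accuracy and will use the optimal methods available".
- **Statistical methods, denoising.** Four techniques are named, and then: "If a more suitable method for denoising the raw data becomes available, that method will be used". The criterion here is suitability; accuracy is not mentioned.
- **Statistical methods, analysis set.** "All research subjects will be included in the analysis". No division into development and evaluation subjects follows.
- **Abstract, Methods and analysis.** One stated aim is "predicting the HAMD scores for an unknown data set". The methods do not say what that data set is, or whether it holds new subjects.
- **Sample size.** Learning curves give about 500 data sets for 90% detection accuracy, 650 for a correlation of about 0.85 and 800 for a mean absolute error of 3. The text discusses how a training set should be composed and sets nothing aside for testing. It also plans to check accuracy part-way through and to adjust the target number.

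**The concern.** Accuracy measured on a finite sample is a noisy estimate. When many pipelines are compared on the same labels and the best is kept, the winner's observed accuracy partly reflects luck. It therefore exceeds the accuracy the same pipeline would show in new subjects. The interview ratings that guide the choice are also the reference standard for both primary outcomes, so the bias would fall directly on the primary result. It would always point towards the targets.

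The stated purpose is software that could be certified as a medical device. What matters is therefore performance in people the model has not seen. The wording as it stands does not secure that figure.

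**Working it through.** **1. The plan's own figures.** 220 + 40 + 40 = 300 subjects, as stated. The earlier study gave 241/86 = 2.80 data sets per subject. At that yield 300 subjects give 300 × 241/86 = 841 data sets. Against the 800 quoted for a mean absolute error of 3, about 41 are left, so the plan has almost no room for a separate test set if 800 are needed for training. The 500, 650 and 800 are read from learning curves in figures that were not available, so they cannot be reproduced.

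**2. Model for the selection effect.** Suppose K candidate pipelines all have the same true accuracy p, and the best observed one is reported. Then:

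- SE = sqrt(p(1 − p)/n_eff), with n_eff = n/DEFF and DEFF = 1 + (2.80 − 1) × ICC
- expected overstatement = c_K × sqrt(1 − ρ) × SE

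Here ρ is the correlation between the pipelines' errors, and c_K is the expected maximum of K independent standard normals: 1.16 for K = 5, 1.87 for K = 20 and 2.51 for K = 100.

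Assumed, because the article gives none of them: K = 5 to 100, ρ = 0 to 0.8, ICC = 0 to 0.6. With n = 800, ICC 0.6 gives DEFF = 1 + 1.80 × 0.6 = 2.08 and n_eff = 800/2.08 = 385. ICC 0 gives n_eff = 800.

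**3. Accuracy.** The low end of each range uses n_eff 800 and ρ = 0.8; the high end uses n_eff 385 and ρ = 0.

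| K | true accuracy 90% | true accuracy 76% |
|---|---|---|
| 5 | +0.6 to +1.8 points | +0.8 to +2.5 points |
| 20 | +0.9 to +2.9 points | +1.3 to +4.1 points |
| 100 | +1.2 to +3.8 points | +1.7 to +5.5 points |

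A harsher n_eff of 300 raises the most extreme corner (76%, K = 100, ρ = 0) to 2.51 × 2.47 = 6.2 points. Most combinations lie between 1 and 5.

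**4. Near the target.** Take true accuracy 88%, K = 20, ρ = 0.5.

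- n_eff 385: SE = sqrt(0.88 × 0.12/385) = 1.66 points, overstatement 1.87 × 0.707 × 1.66 = 2.2, expected report 90.2%.
- n_eff 800: SE = 1.15 points, overstatement 1.5, expected report 89.5%.

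**5. Correlation with HAMD.** The same calculation on the Fisher z scale adds c_K/sqrt(n_eff − 3) to atanh(r) and transforms back. With independent errors, a true r of 0.85 gains 0.011 (K = 5, n_eff 800) to 0.032 (K = 100, n_eff 385). A true r of 0.61 gains 0.025 to 0.074. With ρ = 0.8 the shift in z is multiplied by sqrt(0.2) = 0.45, so the smallest gain falls to about 0.005.

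**6. Against the planned improvement.** The plan looks for 90 − 76 = 14 points of accuracy and 0.85 − 0.61 = 0.24 of correlation. The selection effect is at most about 6 points and 0.07 under these assumptions.

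**7. Not computed.** Overfitting from tuning on the evaluation data, and leakage when one subject's repeated data sets fall on both sides of a split, would add to these figures. The article gives nothing from which to size them.

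**The case against.** The strongest reply is that the article never says selection and evaluation share data. The abstract points the other way by naming an unknown data set. Including all subjects in the analysis is compatible with some of them serving as test subjects. Comparing algorithms and keeping the best is ordinary model development, and the rule would be harmless if accuracy were measured in an inner cross-validation. The article also condenses a fuller protocol, where fold structure and hold-out details may stand.

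Much of this is right, and it rules out stronger readings that a reader might infer:

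- *There will be no untouched test subjects, and the primary result is the maximum of many estimates.* The article is silent on the first, so the second is only conditional. The Primary outcomes section does not define a maximum accuracy as the result, and the 90% is described as a rough target without a pass/fail test.
- *Denoising is chosen by accuracy against the interview labels.* The text says only that a more suitable method may be adopted.
- *The study could not tell whether the model improves on 76% and 0.61.* The computed effect is well below the planned gains of 14 points and 0.24. Its upper end needs uncorrelated errors, which is unlikely for pipelines scored on the same subjects.

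What the reply does not remove is that the article fixes a selection rule and an analysis set, budgets only training data and adds a mid-study look at accuracy. It does not connect any of these to the unseen data promised in the abstract. For a study whose primary outcomes are model estimates, the data on which performance is measured determine what the primary result means. That is more than a detail left for later.

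**Conclusion.** The concern holds in conditional form. The algorithm and the features are selected by highest accuracy with all subjects in the analysis. No evaluation data are defined apart from that selection or from the mid-study check, and the Abstract and Statistical methods are not reconciled on this. If performance is reported from the data used for selection, it is optimistic by roughly 1 to 5 points of accuracy and about 0.01 to 0.07 of correlation.

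These sizes rest on assumed values for the number of pipelines, their error correlation and the effective sample size, and they cover only the picking of a maximum. They are enough to report a true accuracy in the high 80s as meeting 90%. They are not enough alone to produce a rise from 76% to 90%.

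**What to change.** State in Statistical methods that the reported performance for both primary outcomes is the outer-loop estimate of a nested cross-validation in which all data sets from one subject stay in the same fold. Every choice that uses the labels (denoising where it does, features, algorithm, tuning) is made in the inner loop. Give a subject-clustered confidence interval, and say that this is what the abstract's unknown data set means. This reserves no subjects; the cost is computing time.

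Nested cross-validation does not protect against redesigning the candidate list after seeing the mid-study accuracy. An optional addition does: reserve whole subjects, keep them out of selection and of the mid-study check, lock one pipeline per primary outcome and apply it to them once. The cost, at 2.80 data sets per subject:

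| Reserved | Data sets reserved | Left for development |
|---|---|---|
| 20% (60 subjects) | 168 | 841 − 168 = 673 |
| 25% (75 subjects) | 210 | 841 − 210 = 631 |

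Both exceed the 500 quoted for detection and fall below the 800 quoted for a mean absolute error of 3. The 25% split also falls below the 650 quoted for r = 0.85. With 168 reserved data sets, the 95% half-width at 90% accuracy is 1.96 × sqrt(0.09/168) = 4.5 points for ICC 0, and 4.5 × sqrt(2.08) = 6.5 points for ICC 0.6. A hold-out is thus a coarser check, and the nested estimate should come first.
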